# 9. Study design

The study is a monocentric, prospective, interventional, controlled, randomised, double-blind study.

# 10. Inclusion/exclusion criteria

The inclusion criteria are as follows:

- Patients (age > 18 years) with an F2x diagnosis, i.e. schizophrenia, schizotypal disorder, delusional disorder or schizoaffective disorder in inpatient, day-care or outpatient settings in the Department of Psychiatry and Psychotherapy at the SRH Clinic Karlsbad-Langensteinbach , as well as any persons with the above-mentioned disorders who are not treated in the Department of Psychiatry and Psychotherapy at the SRH Clinic Karlsbad-Langensteinbach but who wish to participate in the study.
- Deficiencies in executive functions (verbal working memory, response inhibition, planning ability, cognitive flexibility).

The exclusion criteria are as follows:

- Impaired intelligence (i.e. IQ ≤ 85)
- Neurological diseases that impact cognition
- Drug use within the last 8 weeks
- Patients that are minors
- Patients of legal age who are unable to give their informed consent

# 11. Criteria for withdrawal

## Individual criteria for withdrawal

All study participants can withdraw from the study at any time and without justification and without prejudice to ongoing medical care by withdrawing their consent to participate in the study. Participation in the study may also be discontinued if this becomes necessary for clinical reasons in the Department of Psychiatry and Psychotherapy at the SRH Clinic Karlsbad-Langensteinbach. Participation will also be discontinued if side effects arise as a result of using the DC device, which precludes the stimulation from being continued.

## 11. 2 Criteria for withdrawal of the entire study

None.

# 12. Randomisation procedure

In order to ensure effective double-blinding, randomisation is carried out in collaboration with the manufacturer of the direct current device, the Neuroconn company. The company compiles a list of codes, half of which correspond to verum stimulations and the other half to sham stimulations. The sequence of the codes is then scrambled using randomly generated numbers. Before starting each stimulation, one of these codes is entered, upon which either a verum or a sham stimulation is started. This means that neither the investigator nor the patient knows what type of stimulation is being applied.

# 13. Statistical design

## 13.1 Proposed size of the patient population

The proposed study, will compare mean values (respective average values from the neuropsychological tests) in a two-factor design across independent groups pre-post (2*2 mixed-model design). The statistical hypothesis is as follows:

Statistical hypothesis: There is an interaction between *group*time* in the dependent variable *Performance in the neuropsychological test procedures.*

The size of the patient population required is therefore estimated as a function of the power of the study (1-β), the level of statistical significance (α) and the magnitude of the effect expected (Cohen's d) (Cohen, 1988). The size of the patient population required for the study was estimated using the *G-Power 3* software (Faul, Erdfelder, Lang & Buchner, 2007). To achieve a power of 1-β = 0.9, with a significance level of α = 0.05 and an expected mean effect of d = 0.5, the study needs to enrol n = 23 patients in each group. Assuming a drop-out rate of approximately 10%, the study needs to enrol n = 25 probands in each group. The study will therefore require:

1. 25 patients in the verum stimulation arm
2. 25 patients in the sham stimulation arm

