# 5. Primary and secondary endpoints

The primary endpoint for the aforementioned hypotheses is the improvement of cognitive performance in the area of executive functions in patients with schizophrenia, measured using several standardised neuropsychological testing procedures. There are no other secondary objectives.

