## 6.5 Experimental procedure and time demands on the patients

Following the standard routine diagnostics for inpatients or the first consultation for outpatients (see above), patients will be invited to attend a second consultation. At the beginning of the examination, patients will initially be given a brief explanation about the *DC-Stimulator Mobile*, before application of the device. The device will then be started and the patients asked to complete the “Tower of London”, “N-back verbal”, “Inhib” and “Switch” tests from Schuhfried's Vienna Test System. The selection of test procedures is based on the concept of Miyake's executive functions described above (2000). Since the duration of the tDCS stimulation is shorter than the total time required for the procedures, the stimulation is switched off during the course of the examination. The procedure is finished when test procedures have been completed. The total time required to participate in the study beyond the routine diagnostics is approximately 60 minutes for in-patients. This includes both tDCS stimulation and the processing of neuropsychological procedures. The time required for outpatients is approximately 2 hours for the first consultation and approximately 1 hour for the second consultation, i.e. a total of 3 hours for the entire study period.

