## 13.2 Statistical analysis

The statistical analysis will be performed on pseudonymised data. Variables of patient characteristics and dependent variables will be analysed using descriptive statistics. For the inferential statistical evaluation of the data, mean value comparisons between the two groups will be performed using pre/post comparisons. Each of the dependent variables will be analysed using on a two-factor mixed-model ANOVA with the between-subject factor group (*verum stimulation* vs. *sham stimulation*) and the within-subject factor time interval (*pre* vs. *post*). Any potential interactions will be further explored by using *a priori* planned comparisons (e.g. t-tests). Where appropriate, several dependent variables will be grouped together to reduce the number of analyses required. If the assumptions for parametric analyses are not satisfied (normal distribution of the error components, homoscedasticity of the error variances, independence of the measured values), the means of individual dependent variables will be compared using a nonparametric test (e.g. Mann-Whitney U-test). If multiple statistical methods are used (t-tests, Mann-Whitney U-tests), the alpha level will be adjusted (Bonferroni correction or Bonferroni Holm procedure) to reflect the overall alpha. The magnitude of individual effects will also be determined (Cohen, 1988) to quantify any potential differences obtained.

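### Section 13.1 sizes one interaction test at α = 0.05, but section 13.2 tests several outcomes and leaves open whether their interactions are alpha-adjusted, so 90% power and the overall alpha hold together only for a single composite

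*Protocol*

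**What the plan says.** - **Sizing (section 13.1).** The design is a "two-factor design across independent groups pre-post (2*2 mixed-model design" and the hypothesis is a group-by-time interaction in one dependent variable, named in the singular. The inputs are "To achieve a power of 1-β = 0.9, with a significance level of α = 0.05 and an expected mean effect of d = 0.5". The result is 23 per group, raised to 25 for about 10% drop-out. Multiplicity is not mentioned.
- **Endpoint (section 5).** The primary endpoint is improvement in executive function, "measured using several standardised neuropsychological testing procedures". No number of outcomes is fixed.
- **Tests (section 6.5).** During the session patients "complete the “Tower of London”, “N-back verbal”, “Inhib” and “Switch” tests". How many scores each test contributes is not stated.
- **Analysis (section 13.2).** Every dependent variable gets its own two-factor mixed ANOVA. Some variables may be combined if that seems suitable. If several methods are used, with t-tests and Mann-Whitney tests given as the instances, "the alpha level will be adjusted (Bonferroni correction or Bonferroni Holm procedure) to reflect the overall alpha".

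**The concern.** The sizing and the analysis do not clearly use the same decision rule. The printed 90% belongs to one test at the full 0.05, while the analysis plan looks at several outcomes one by one and speaks of protecting an overall alpha. The adjustment sentence does not say whether it reaches the interactions.

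Something is lost on either reading. If the interactions are adjusted, a non-significant result on one test would be read against a 10% type II error that does not apply. If they are not, a significant result on one of several tests would be read against a 5% error that does not apply. The first case matters most when only one domain responds. The protocol's own literature summary (section 3.3.2) makes that plausible: it reports benefit on verbal working memory and none yet shown for planning or response inhibition.

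**Working it through.** **Inputs.** From section 13.1: α = 0.05, power 0.9, d = 0.5, two groups, two time points, 23 per group (N = 46). From section 6.5: four named tests. Assumed, because the protocol does not print them: d = 0.5 entered as f = d/2 = 0.25, and a pre-post correlation ρ = 0.5.

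**Step 1: reproduce the printed sample size.** For the within-between interaction the noncentrality is λ = f² × N × m / (1 − ρ), with m = 2 measurements and an F test on 1 and N − 2 degrees of freedom.

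- N = 46: λ = 0.0625 × 46 × 2 / 0.5 = 11.5; power 91.2%.
- N = 44: λ = 11.0; power 89.97%, just short of 90%.

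The smallest even N reaching 90% is therefore 46, or 23 per group, which matches the protocol. Other assumed correlations do not give it: the total N would be 88 (ρ = 0), 62 (0.3), 36 (0.6) or 28 (0.7).

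**Step 2: if the interactions are adjusted.** Keep N = 46 and λ = 11.5 and replace α by 0.05/k. This is the Bonferroni threshold and also the first Holm step.

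| Tests k | α/k | Power per test, printed n | Power per test if the base is exactly 90% |
|---|---|---|---|
| 1 | 0.05 | 91.2% | 90% |
| 2 | 0.025 | 85.4% | 83.6% |
| 3 | 0.0167 | 81.2% | 79.2% |
| 4 | 0.0125 | 78.0% | 75.8% |
| 5 | 0.01 | 75.4% | 73.0% |
| 8 | 0.00625 | 69.6% | 67.0% |

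The last column solves for the λ that gives exactly 90% at α = 0.05 with 44 degrees of freedom (λ = 10.99). It needs no assumption about how d was standardised. With all 25 per group evaluable (N = 50), the four-test figure on the reproducing inputs is 82.2%. Reaching 90% at 0.0125 would take N = 62, or 31 per group.

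**Step 3: Holm.** The interaction test is equivalent to a two-sample t-test on change scores; λ = 11.5 corresponds to 1.0 SD of change, since (23/2) × 1.0² = 11.5. In 20,000 simulated trials with this effect on all four outcomes, average per-test power under Holm is 88.5%, 87.1%, 86.4% and 85.0% for between-outcome correlations of 0, 0.3, 0.5 and 0.8. From an exact 90% base the corresponding range is about 84-87% (correlations 0 to 0.6). If only one outcome responds, Holm gives little more than Bonferroni.

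**Step 4: if the interactions are not adjusted.** Power per test stays at 91.2%. For k independent tests, familywise error is 1 − 0.95^k:

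- k = 2: 1 − 0.9025 = 9.75%
- k = 4: 1 − 0.8145 = 18.5%
- k = 8: 1 − 0.6634 = 33.7%

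Positive correlation between outcomes would lower these values.

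**Step 5: a single composite.** With one outcome there is one test at 0.05, and both printed figures stand.

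**The case against.** A reader might infer that section 13.2 firmly adjusts alpha across the outcomes, so that the trial has about 76% power and the protocol contains a calculation error. The text does not support this, for four reasons.

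- **The rule is conditional.** It names t-tests and Mann-Whitney tests, which serve as follow-up comparisons or as the nonparametric fallback. It does not name the ANOVA interaction. Read literally, the interaction stays at 0.05 and its power is untouched. This stands, and it is why the finding has two branches.
- **One outcome may be meant.** Section 13.1 names a single dependent variable and section 13.2 allows grouping. This stands as a possibility. But section 13.2 also gives each dependent variable its own ANOVA, and no composite is defined.
- **Four is an inference from section 6.5.** Grouping could lower the number and several scores per test could raise it. This stands, so a range is shown; every value from two tests upward is below 90%.
- **The printed n reproduces.** The point is therefore one of consistency and multiplicity, not arithmetic. The 76% belongs to a base of exactly 90%; on the inputs that reproduce 23 per group the figure is 78%. Neither is the trial's true power, because both rest on an effect and a correlation that were assumed. If d = 0.5 were meant in SDs of change, power at 23 per group would be about 38% unadjusted and 19% at 0.0125.

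It may also be said that both procedures control the overall error and that the choice can wait for a statistical analysis plan, which is not at hand. That is fair as far as validity goes. But Holm controls the same error and never rejects less, so leaving Bonferroni open gains nothing.

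**Conclusion.** The concern holds in conditional form. The sizing covers one interaction at an unadjusted 0.05, the analysis covers several, and the protocol does not say whether the adjustment applies to them.

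- **Adjusted:** with four tests, power per test at the first threshold drops by about 13 points (91.2% to 78.0%), and the chance of missing the sized effect on a given test is about 22% rather than 9%. Holm recovers part of this, to about 84-88%, only if all four outcomes respond equally.
- **Not adjusted:** power is as printed, but the overall alpha is about 18.5% for four independent tests.

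Both printed figures survive only with a single composite, which the protocol permits but does not fix.

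The percentages from the printed n rest on f = 0.25 and ρ = 0.5. At ρ = 0.7 the adjusted four-test power would be 95.8%, but that correlation would have given a total N of 28 and not 46, so it cannot be the basis of the printed number.

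**What to change.** **Section 13.2.** State that the adjusted family is the group-by-time interactions on the four tests named in section 6.5, or on the grouped outcomes if the grouping is specified in advance. Replace the open choice of procedure with Holm.

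**Section 13.1.** Keep 25 per group. Beside the unadjusted power, give the per-test power at the first Holm step: 0.05/4 = 0.0125, about 78% with 23 evaluable per group. Print the assumed pre-post correlation and say that the figure is per test. If grouping leaves a different number of outcomes, use that number in place of four.

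**Cost.** Protocol wording and one recalculation, with no extra patients. The downside is a less favourable stated power.

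### The stated 90% power for d = 0.5 with 23 patients per arm does not follow from the protocol's inputs; 23 per arm matches a 1.0 SD difference in change

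*Protocol*

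**What the plan says.** Protocol section 13.1 sets the statistical hypothesis as "There is an interaction between *group*time* in the dependent variable" of neuropsychological test performance, in a 2x2 mixed design (verum or sham, pre or post). Section 13.2 analyses each dependent variable by a "two-factor mixed-model ANOVA with the between-subject factor group" and a pre/post within-subject factor.

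The sample size in section 13.1 is said to depend on power, alpha and "the magnitude of the effect expected (Cohen's d"). The software is named: "The size of the patient population required for the study was estimated using the *G-Power 3* software". Power is set at 0.9 and alpha at 0.05, and the resulting number is given as follows: "an expected mean effect of d = 0.5, the study needs to enrol n = 23 patients in each group". Enrolment is then raised to 25 per arm for drop-out.

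The section does not say which SD standardises d, which G*Power routine was used, what pre/post correlation was entered, or whether the test is one- or two-sided.

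**The concern.** In a 2x2 mixed design the interaction has one degree of freedom, and its F-test is the same test as a two-sided two-sample t-test on the change scores. The quantity being tested is therefore the between-arm difference in change. A reader takes Cohen's d = 0.5 as half a standard deviation between the arms, and 23 per arm is far too few to detect that with 90% power unless pre and post scores are very highly correlated.

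This is a figure that the protocol itself states, so it is not a detail left to an analysis plan. An ethics committee and later readers rely on it. A non-significant result set against a claimed 90% power for a medium effect would look more informative than the design allows.

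**Working it through.** **Inputs from section 13.1:** power 0.90, alpha 0.05, d = 0.5, two equal arms, 23 evaluable per arm. The two-sided test follows from the ANOVA F-test in section 13.2. The pre/post correlation (rho) is not given, so a range is shown.

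**Step 1. Can 23 per arm be reproduced?** G*Power's repeated-measures within-between interaction routine, with N patients in total and m = 2 time points, uses

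lambda = f² × N × m / (1 − rho).

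The two-group rule f = d/2 turns d = 0.5 into f = 0.25. With rho = 0.5:

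- N = 44: power 0.8997
- N = 46: lambda = 0.0625 × 46 × 2 / 0.5 = 11.5, power 0.9125

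The smallest even total reaching 90% is 46, which is 23 per arm. This reproduces the protocol's number, but only with f = 0.25 and rho = 0.5, neither of which the protocol states.

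**Step 2. What effect does f = 0.25 mean here?** In a 2x2 interaction, f = 0.25 means that the four cell means deviate by ±0.25 SD. The between-arm difference in change is then 4 × 0.25 = 1.0 SD. As a check, the t-test on change has lambda = d² × n / 2. With n = 23 this is 11.5 × d², which equals 11.5 when d = 1.0. The exact t-test at d = 1.0 gives 0.8997 with 22 per arm and 0.9125 with 23, the same values as in step 1.

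**Step 3. Power for d = 0.5 on the change score.** The noncentrality is 0.5 × √(23/2) = 1.70 on 44 degrees of freedom.

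- 23 per arm: 38.2% (simulation of 20,000 trials at rho 0.5: 37.7%)
- All 25 enrolled per arm: 41.0%
- One-sided, 23 per arm: 51.0%
- Needed for 90%: 86 per arm two-sided, 70 one-sided

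**Step 4. Power if d = 0.5 is in raw-score SDs.** The change score has SD √(2(1 − rho)) in raw units, so the effect on the change scale is 0.5 / √(2(1 − rho)).

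| rho | effect on change scale | power, 23 per arm | n per arm for 90% |
|---|---|---|---|
| 0.3 | 0.423 | 28.9% | 119 |
| 0.5 | 0.500 | 38.2% | 86 |
| 0.7 | 0.645 | 57.2% | 52 |
| 0.8 | 0.791 | 74.6% | 35 |
| 0.85 | 0.913 | 85.7% | 27 |
| 0.875 | 1.000 | 91.2% | 23 |

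Power passes 50% at rho of about 0.64 and 90% at about 0.87.

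**Step 5. Effect of adjusting alpha.** Section 6.5 lists four tests at the stimulation session. If alpha were divided by four (an assumption), it would be 0.05/4 = 0.0125. Power at 23 per arm would be:

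| difference in change (SD, rho 0.5) | alpha 0.05 | alpha 0.0125 |
|---|---|---|
| 1.0 | 91% | 78% |
| 0.84 | 80% | 60% |
| 0.5 | 38% | 19% |

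**The case against.** The best defence is that section 13.1 leaves the metric of d open. If d is in raw-score SDs and rho is about 0.87 or higher, 23 per arm does give 90%. Nothing in the protocol rules that out. It stands as a condition on the finding, but it does not rescue the statement: the correlation is neither given nor justified. The pre-test is taken at an earlier consultation and the second test is started under stimulation (sections 6.4 and 6.5), so so high a value cannot simply be assumed.

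Four stronger readings are tempting, and the documents do not support them.

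- *That the sponsor entered f = 0.25 and rho = 0.5.* The exact match at 46 makes this likely, but it is an inference. In the same routine, f = 0.125 (0.5/4) with rho = 0.875 also gives 46. The mismatch with d = 0.5 does not depend on which was used.
- *That power is 38% without qualification, or that a null result is more likely than not if the true effect is d = 0.5.* Both need conditions. The 38% holds for d on the change score, or on raw scores at rho 0.5. The null is the likelier outcome for d on the change score, or for raw-score d with rho below about 0.64. At 0.7 and 0.8 a significant result is more likely.
- *That the sponsor will read a null result as showing that tDCS does not work.* The protocol gives no such rule of interpretation.
- *That the drop-out allowance is an error.* The text reads "Assuming a drop-out rate of approximately 10%, the study needs to enrol n = 25 probands in each group". Going from 25 to 23 is a loss of 2/25 = 8%, and 23/0.9 = 25.6. Given the word 'approximately', and power of 0.8997 even with 22 per arm at a 1.0 SD difference, this is immaterial. Changing the assumed rate to fit the enrolled number would not be an improvement.

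The adjusted-alpha figures are also conditional. Section 13.2 ties the Bonferroni or Holm correction to t-tests and Mann-Whitney tests, so its use on the four interaction tests is assumed.

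**Conclusion.** The power statement is wrong as written: power 0.9, alpha 0.05 and d = 0.5 do not lead to 23 per arm for the stated hypothesis. On the change-score reading the requirement is 86 per arm, and 23 per arm has about 38% power. On the raw-score reading, power runs from 29% to 75% for correlations of 0.3 to 0.8, and the claim holds only from about 0.87 upward. A one-sided test does not close the gap on the change-score reading. These figures assume a single two-sided test at 0.05, 23 evaluable per arm, normal errors and equal variances at both times and in both arms. Any adjustment of alpha over several tests lowers them.

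The finding concerns the stated power. It does not show that the trial must enrol more patients.

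**What to change.** Keep the sample size and restate the power in section 13.1. Name the effect-size metric (including which SD standardises it), the G*Power routine and the assumed pre/post correlation. Possible wording:

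> With 23 evaluable patients per arm, for a single unadjusted two-sided test at alpha 0.05 and an assumed pre/post correlation of 0.5, power is about 91% for a between-arm difference in change of 1.0 SD, 80% for 0.84 SD and 38% for 0.5 SD. Power is lower if alpha is adjusted over several tests (assuming four tests at alpha 0.0125: about 78%, 60% and 19%).

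The correlation of 0.5 is a placeholder that reproduces the existing number. If the sponsor has a supported value, it should be used and the figures recalculated. When a non-significant result is interpreted, the trial should not be described as having 90% power for d = 0.5.

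The cost is one reworded paragraph and a less favourable stated power. No extra patients are needed, and the drop-out sentence can stay as it is.

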## 13.2 Statistical analysis

The statistical analysis will be performed on pseudonymised data. Variables of patient characteristics and dependent variables will be analysed using descriptive statistics. For the inferential statistical evaluation of the data, mean value comparisons between the two groups will be performed using pre/post comparisons. Each of the dependent variables will be analysed using on a two-factor mixed-model ANOVA with the between-subject factor group (*verum stimulation* vs. *sham stimulation*) and the within-subject factor time interval (*pre* vs. *post*). Any potential interactions will be further explored by using *a priori* planned comparisons (e.g. t-tests). Where appropriate, several dependent variables will be grouped together to reduce the number of analyses required. If the assumptions for parametric analyses are not satisfied (normal distribution of the error components, homoscedasticity of the error variances, independence of the measured values), the means of individual dependent variables will be compared using a nonparametric test (e.g. Mann-Whitney U-test). If multiple statistical methods are used (t-tests, Mann-Whitney U-tests), the alpha level will be adjusted (Bonferroni correction or Bonferroni Holm procedure) to reflect the overall alpha. The magnitude of individual effects will also be determined (Cohen, 1988) to quantify any potential differences obtained.

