# 6. Study related procedures/study timeline

## 6.1 Recruitment of patient population

The study will be conducted in the Department of Psychiatry and Psychotherapy at the Karlsbad-Langensteinbach Clinic in Germany. The patient population will be recruited through the wards. Patients will be invited to participate in the study during the routine admission diagnostics assessment. During this first consultation, the patient's inclusion/exclusion criteria will be reviewed and patients will be provided with information about the study. Should the patient give his/her consent, an appointment is then scheduled for the examination *per se*.

In addition to hospitalised patients, we will also recruit from out-patients All patients interested in participating in the study will first be invited to an initial interview, during which the patients' inclusion/exclusion criteria will be reviewed and they will be provided with information about the study. If patients wish to participate in the study, they will undergo some psychological tests and fill in several questionnaires after the interview. These are the same procedures that in-patients also undergo as part of routine clinical diagnostics. An appointment for the actual examination is then arranged to proceed with the stimulation protocol using the tDCS device.

The proposed study will not involve initiating patient medical drug treatments, nor will the proposed study change any existing medical drug treatments taken (e.g. dose changes). Participation in the study neither requires a change of medication nor will it impede a clinically necessary modification.

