## 6.4 Standardised and normalised neuropsychological test procedures to assess cognitive performance:

All patients will undergo the COGBAT® test set (Aschenbrenner, Kaiser, Pfüller, Roesch-Ely & Weisbrod, 2012) as part of routine clinical diagnostics or during an additional outpatient consultation before beginning the examination. This test set includes a compilation of key neuropsychological parameters to assess the cognitive status of patients with mental disorders. It covers the following parameters: attention, memory, executive functions and processing speed. Specific focus will be placed on performance in the subtests addressing planning ability (“Tower of London”), verbal working memory (“Nback-Verbal“) and response inhibition (“INHIB”). The “SWITCH” test from the Vienna Test System will also be used to assess cognitive flexibility. See Table 1 for an overview of the methods used.

Table 1: Overview of diagnostic, therapeutic and interventional procedures

| **Clinical diagnostics and psychopathology**   - Sociodemographic interview - SCID-I (Wittchen, Zaudig & Fydrich, 1997) - SCID-II - Montgomery-Asberg Depression Rating Scale (MADRS, Montgomery & Asberg, 1979) - Beck Depression Inventory (BDI-II, Hautzinger, Keller & Kühner, 2006) - Personality style and disorder inventory (PSSI, Kuhl & Kazén, 2009) - Inventory of social competence (ISK, Kanning, 2009) - Emotional Competence Questionnaire (EKFS, Rindermann, 2009) - Cognitive performance questionnaire* (FLei, Beblo, Kunz, Lautenbacher, Albert & Aschenbrenner, 2011) |
| --- |
| **Premorbid intelligence**   - MWT-B (Lehrl, 2005) (German multiple choice word selection test) |
| **Neuropsychological diagnostic procedures**  **Vienna test system**  *Information processing speed*   - Trail Making Test Langensteinbach Version*   *Attention*   - Divided attention WAFG test* - Alertness-WAFA test*   *Memory*   - FGT (Figural Memory Test)*   *Executive functions*   - Working memory N-back verbal* - Inhibition-INHIB Go-Nogo* - Cognitive Flexibility Trail Making Test Langensteinbach Version* - Cognitive Flexibility- SWITCH - Convergent Planning-Tower of London-Freiburg Version* |
| **Neurophysiological stimulation**   - DC-Stimulator Mobile, *NeuroConn* |

*Cognitive basic testing from the Vienna Test System (CogBat)

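### Follow-up t-tests in Section 13.2 are not confined to verum-versus-sham contrasts; pre/post tests within an arm could show improvement through regression to the mean and practice alone

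*Protocol*

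**What the plan says.** **Selection.** Section 10 of the Protocol requires "Deficiencies in executive functions (verbal working memory, response inhibition, planning ability, cognitive flexibility" and closes the list there. It gives no test, score or cut-off, and does not say whether one deficit suffices or all four are needed.

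**Pre scores.** Section 6.4 on the neuropsychological procedures says "All patients will undergo the COGBAT® test set" before the examination. Of this set, "Specific focus will be placed on performance in the subtests addressing planning ability", verbal working memory and response inhibition. SWITCH is added for cognitive flexibility; Table 1 does not mark it as part of CogBat.

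**Post scores.** At the second consultation (Section 6.5), "The device will then be started and the patients asked to complete the" same four tests: Tower of London, N-back verbal, INHIB and SWITCH. No other testing before stimulation is described, so the earlier scores have to serve as pre.

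**Analysis.** The only statistical hypothesis (Section 13.1) is the group-by-time interaction. Section 13.2 announces that "mean value comparisons between the two groups will be performed using pre/post comparisons", by a two-factor mixed ANOVA for each dependent variable. It continues: "Any potential interactions will be further explored by using" a priori planned comparisons, with t-tests as the example. Whether these are between arms or within an arm is not said.

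**The concern.** Patients chosen because they score low on a test tend to score higher when retested, with no treatment at all, and repeating the same test usually adds a practice gain. Both arms share these gains, so they cancel from a verum-minus-sham contrast. They do not cancel from a pre/post comparison inside one arm.

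The t-tests of Section 13.2 lead easily to that second kind of comparison. In a 2×2 design a between-arm t-test on change is the interaction itself (t² = F), so it cannot explore the interaction further. What remains is verum against sham at one time point, or pre against post within an arm. At pre, randomised arms differ only by chance. Nothing in Section 13.2 rules out the within-arm tests.

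The wording elsewhere adds to the risk. Section 5 defines the primary endpoint as improvement, and the Section 4 hypothesis predicts improvement, in neither case relative to sham. A gain within the verum arm would satisfy both as worded. At stake is a report that verum improved and sham did not, which is not a test of the difference between them, or a one-arm gain quoted as the size of the tDCS effect.

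**Working it through.** **1. The plan's own figure.** Inputs from Section 13.1: power 0.90, α 0.05, d = 0.5 (so f = 0.25), two groups, two time points. A pre/post correlation of 0.5 is my assumption, as none is stated. For the interaction of a repeated-measures ANOVA, λ = f²·N·m/(1 − ρ). With N = 46, λ = 0.0625 × 46 × 2/0.5 = 11.5 and power is 0.912; with N = 44 it is 0.8997. The stated 23 per group is reproduced, so the sample size rests on the interaction, a between-arm contrast.

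**2. Regression to the mean when the test analysed is also the test used for selection.** Assumptions: cut-off 1 SD below the norm; retest correlation r of 0.5, 0.7 or 0.8; no stimulation effect; no practice effect.

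- Expected gain = (1 − r)·φ(c)/Φ(c), where c is the cut-off measured from the source population's mean.
- Source population at the norm (c = −1): φ/Φ = 1.525.
- Source population 1 SD below the norm (c = 0): φ/Φ = 0.798.
- Variance of the selected pre score: 1 − 1.525 × (1.525 − 1) = 0.199, and 1 − 0.798² = 0.363.
- SD of change = √[(1 − r)²·v + 1 − r²], with v one of these two variances.

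Example, source at the norm, r = 0.7: gain 0.3 × 1.525 = 0.46; SD √(0.09 × 0.199 + 0.51) = 0.727; standardised gain 0.63. With n = 23, 0.63 × √23 = 3.02, against a critical t of 2.07.

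| Source population | r | Spurious gain (SD) | One-arm paired t-test significant for improvement, n = 23 |
|---|---|---|---|
| At the norm | 0.5 | 0.76 (0.77 simulated) | 98% |
| At the norm | 0.7 | 0.46 | 82% |
| At the norm | 0.8 | 0.31 | 64% |
| 1 SD lower | 0.5 | 0.40 | 52% |
| 1 SD lower | 0.7 | 0.24 | 32% |
| 1 SD lower | 0.8 | 0.16 | 22% |

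The percentages are simulated (4,000 trials per row). The nominal rate in that direction is 2.5%.

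**3. Other entry rules, same cut-off and correlations (simulated).**

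- *A deficit on any one of four tests suffices.* The result depends on how scores move together, here with an assumed inter-test correlation of 0.3 to 0.5. If a patient's low day affects all tests, the gain per test is 0.11 to 0.37 SD (source at the norm) or 0.03 to 0.13 SD (1 SD lower). If errors are independent between tests, it is 0.06 to 0.15 SD or 0.02 to 0.04 SD, and a one-arm test is significant in only about 3% to 9% of trials.
- *Deficits on all four are needed* (independent errors). Gain 0.10 to 0.51 SD; a one-arm test is significant in 11% to 73% of trials.

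**4. The interaction test.** In every scenario, with no stimulation effect, it rejected in 4.5% to 6.0% of trials (nominal 5%). It is not affected.

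**5. Precision of the alternative.** Without selection, the variance of the adjusted between-arm difference relative to the change-score difference is (1 − r²)/[2(1 − r)] = (1 + r)/2, which is 0.75, 0.85 and 0.90. With selection it is (1 − r²)/[(1 − r)²·v + 1 − r²]. This runs from 0.75/(0.25 × 0.363 + 0.75) = 0.89 to 0.36/(0.04 × 0.199 + 0.36) = 0.98. Estimating the slope with 46 patients costs about 1/(46 − 4) = 2.4% of variance, so the worst of these cases is close to break-even and the others gain.

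**The case against.** The strongest reply is that the Protocol plans no such test. The sentence on mean comparisons speaks of the two groups, the named nonparametric fallback (Mann-Whitney) compares independent groups, and no paired test appears. Follow-ups are there to explore an interaction. If they run only after a significant one, the chance of a false interaction together with a significant verum gain is below about 5%. All of this stands: the within-arm test is one reading of an open sentence, and the primary test is sound. It does not close the sentence, though. Nor does gating protect the size of a reported effect: if the true difference in change were 0.5 SD and the regression gain 0.46 SD, the verum arm would be expected to improve by 0.5 + 0.46 = 0.96 SD.

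Four stronger readings are tempting and are not supported.

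- *Selection was made on the very scores that serve as pre.* Section 10 names no test. For outpatients, Section 6.1 describes an interview "during which the patients' inclusion/exclusion criteria will be reviewed and they will be provided with information about the study", and says of those who wish to take part that "they will undergo some psychological tests and fill in several questionnaires after the interview". SWITCH also stands outside CogBat.
- *Within-arm tests will show improvement.* Under an any-of-four rule the gain can be negligible.
- *The artefact is as large as the planned effect.* Most of the figures above lie below 0.5. Moreover, d = 0.5 is planned for the interaction, not for a gain in one arm.
- *In-patients recover between the visits.* Section 3.2 describes these cognitive disorders as largely independent of acute symptoms and stable, and any recovery would occur in both arms.

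It may also be said that the choice of follow-up contrast belongs in a statistical analysis plan. That is fair for detail, but Section 13.2 already describes the follow-ups as planned a priori, and a better analysis is available from data already collected.

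**Conclusion.** The concern holds as a weakness in the follow-up analysis, not as a flaw in the primary test. The selected domains match the tested domains, the earlier scores are the only available pre values, and Section 13.2 leaves room for within-arm pre/post t-tests that cannot separate stimulation from regression to the mean and practice.

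The spurious gain from regression alone is about 0.03 to 0.77 SD (0.02 at the lowest if test errors are independent). This rests on an assumed cut-off of 1 SD below the norm, retest correlations of 0.5 to 0.8, and a source population at the norm or 1 SD below it. The Protocol gives none of these. Practice gains would come on top and are not quantified. The group-by-time interaction and the sample size of 23 evaluable patients per group are untouched.

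**What to change.** In Section 13.2, state that:

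- for each test, inference and any follow-up rest on the verum-minus-sham difference in post score, adjusted for the pre score (ANCOVA), with a 95% CI;
- pre/post change within each arm is reported descriptively, without p-values;
- the main effect of time is not read as evidence of a stimulation effect.

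This takes a few sentences. The pre score is already collected, so there is no added patient burden, no new data and no change in sample size. Precision is at least as good as that of the pre/post interaction, apart from the small-sample cost of about 2% shown above.
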